#### Quality of life

Quality of life (generic) will be assessed using a short quality of life questionnaire for children EQ-5DY.^24^ The questions will be included in the baseline and follow-up questionnaires.

#### Other confounding variables

At baseline, we will also ask children to report on some of the basic sociodemographic details on the questionnaire. These will include age, gender, household amenities, family structure, cohabiting smokers—including parents, pet ownership, overcrowding—number of rooms and residents, built environment, neighbourhood, presence of mould/moisture in the child's home, and use of gas for cooking or gas/kerosene/oil heater. Furthermore, we will include information on children's medical history (particularly asthma and chest infections) and use of any regular medications.

#### Absenteeism and academic performance

Each participating school will be asked to provide a report on the academic performance of participating children using the Academic Performance Questionnaire (APQ).^25^ This is a 10-item questionnaire to be completed by teachers. Using four-point and five-point ordinal scales, it measures a child's performance in reading, mathematics, writing and homework. This questionnaire will be completed at baseline and at all follow-ups. In addition, schools will also be requested to provide a record of child's absenteeism from school including the number of days missed every month in between two assessments.

#### Fidelity index

The research team will use a fidelity index, mapped onto the behaviour change techniques that underpin SFI, to assess intervention adherence. This will be in the form of a checklist, which will be used to monitor the delivery of SFI sessions. One of the members of the research team will attend all SFI sessions and using the above checklist will score fidelity to SFI.

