Two 45 min sessions delivered over 2 days by schoolteachers. The duration of these sessions is consistent with regular school lessons. Each session consists of a range of educational activities including classroom presentations, quiz, interactive games, storytelling and role-play—vicarious learning techniques are utilised in many of these activities. The presentation, quiz and games are designed to increase pupils’ knowledge about SHS and related harms, and motivate them to follow three easy steps to make their homes smoke-free. The storybook and role-play focuses on enhancing children's negotiation skills, building their confidence within the Bangladeshi cultural context. While the storybook depicts the challenges of negotiating with elders, the role-play has hypothetical scenarios where children had an opportunity to practise and demonstrate how and when they can discuss and negotiate with elders to persuade them not to smoke inside homes.A set of four refresher sessions (15 min each) to reinforce key messages delivered in the initial sessions, to be delivered once a week over 6–7 weeks after the two initial sessions. During each session, the teacher reminds children of the key points of the main session by asking questions (5–7 min), and then encouraging students to share their experiences of whether they could initiate discussion at home, what challenges they faced, what is their plan to do next and what would be the best way to convince the elders (8–10 min). The length of these sessions is consistent with the duration of the school assembly.Children are given a promise form that contains pictorial and written messages on the hazards of SHS, a pictorial step-guide for families on how to make their homes smoke-free and a tear-off slip to make a commitment to impose smoking restrictions at home. Children take promise forms to their parents, show them the messages and negotiate with them to ‘sign-up’ to the SFI ‘promise’ form. One of the implications is that even if parents are non-smokers, they will not allow other smokers (residents and visitors) to smoke inside homes. In addition to delivering the intervention, teachers will also be trained to support children in this process.

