### AEs procedures

We are expecting a minimal number of adverse and no serious AEs (SAEs) during the study. SFI is an educational intervention and has been very well received in our previous studies^17^ without leading to any directly related AEs. Nevertheless, there will be a vigilant surveillance system in place for AEs occurring during the course of the trial with particular emphasis on identifying, recording, reporting and managing any SAEs. We will sensitise schoolteachers to look for signs of any AEs resulting from the interactions between children and their parents. We will also encourage children and parents to report any related adversities.

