#### Definitions

##### Adverse event

An AE is any untoward clinical event in a trial participant, which may or may not be related to the study intervention. The clinical event could be an unfavourable and unintended symptom, sign, medical condition, abnormality or disability that has appeared or worsened during the course of the trial, regardless of a causal relationship to the study intervention.

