#### Detecting, recording and reporting of AEs and SAEs

In the event of any AE reported by the child, their parents/carers or schoolteachers, the research assistant will complete an AE form, which will include medical diagnosis, if relevant and available. The research assistant will also call the trial manager on the same day providing a verbal report of the event. The trial manager will ensure that the event is classified appropriately after receiving the verbal report. All AEs will be reported to the principal investigator, Bangladesh (RH) within 3 days of detection. AE data will be collated and reported to the trial sponsors and National Bioethics Committee at six monthly intervals. These must also be reported to the Study Operational Committee (SOC) and the Independent Trial Steering Committee (ITSC) at their regular meeting. All AEs that have the potential to develop into SAEs will be followed to resolution or stabilisation and reported as SAEs if they become serious. All SAEs must be reported to the principal investigator within 24 h of detection and should also be reported to the trial sponsors and National Bioethics Committee within three working days. All serious events must also be reported to all study investigators and the chair of the ITSC within 3 days. The chief investigator will have the overall responsibility to ensure that all AEs are reported according to the above protocol.

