#### Statistical analysis

We will conduct a preliminary analysis summarising: participant (individual and cluster) characteristics; attrition rates; likely estimates of effect and ICC for the outcomes. This will also include a comparison between participants with detectable and zero levels of cotinine at baseline. Although determining differences in the outcomes between the two arms is not the purpose of this study, we will summarise outcomes at both cluster and individual levels using an intention-to-treat principle and estimate 95% CIs for any differences. All analyses will be conducted using SAS 9.4 (Institute Inc, Cary, North Carolina, USA).

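### Adverse events are likely to be found more completely in the intervention arm: recording relies on spontaneous reports, and only that arm has six researcher-attended sessions

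*Protocol article*

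**What the plan says.** All references are to the protocol article.

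- **Sessions.** Smoke free intervention describes "Two 45 min sessions delivered over 2 days by schoolteachers" and "A set of four refresher sessions (15 min each) to reinforce key messages delivered in the initial sessions". In each refresher the teacher spends 8–10 minutes "encouraging students to share their experiences of whether they could initiate discussion at home, what challenges they faced". Under Treatment as usual, control schools receive the intervention only once the trial is complete.
- **Observer.** Fidelity index: "One of the members of the research team will attend all SFI sessions and using the above checklist will score fidelity to SFI".
- **How an AE is recorded.** "In the event of any AE reported by the child, their parents/carers or schoolteachers, the research assistant will complete an AE form" (Detecting, recording and reporting of AEs and SAEs).
- **What is asked for.** AEs procedures says that teachers will be made alert to AEs arising from exchanges between children and parents, and adds: "We will also encourage children and parents to report any related adversities".
- **What counts.** The definition of an AE applies "regardless of a causal relationship to the study intervention".
- **Common contacts.** Data collection sets follow-up at months 2, 6 and 12. Table 1 has no AE row.
- **Use.** AE frequency and nature is the last pilot research question in the Introduction, and AEs are among the estimates listed in the Abstract. Statistical analysis says that "we will summarise outcomes at both cluster and individual levels using an intention-to-treat principle and estimate 95% CIs for any differences", without naming AEs.

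**The concern.** When AEs are found only by someone choosing to report them, the count depends on how often people have an occasion to speak and how they are prompted. Both differ by arm here. Intervention children have six extra occasions with research staff in the room, and four of these invite them to describe difficulties at home. That is close to the one harm the AE section singles out, trouble between children and parents. Asking families for *related* adversities also works unevenly: a control family has received no intervention for an event to be related to, yet its events count under the definition.

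If more AEs are recorded in SFI schools, the planned data could not separate real conflict at home from more listening. A false signal of harm, or a real one explained away, could then be carried into the definitive trial.

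**Working it through.** The plan gives no AE rate or detection figure, so there is nothing of its own to reproduce. The check is a count of contacts followed by an illustration.

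**1. Contacts.** Sessions: 2 + 4 = 6, or 2 × 45 + 4 × 15 = 150 minutes in the intervention arm against 0 in control. Visits common to both arms for a child who is followed up: 3. Total: 9 against 3. Teacher and head-teacher interviews (Qualitative evaluation) also take place only in intervention schools.

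**2. Equal true rates, disclosure probability q at each contact.** q is an assumption, and contacts are taken as independent. P(found) = 1 − (1 − q)^k, with k = 9 or 3.

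| q | Control (k = 3) | Intervention (k = 9) | Ratio |
|---|---|---|---|
| 0.02 | 0.059 | 0.166 | 2.83 |
| 0.05 | 0.143 | 0.370 | 2.59 |
| 0.10 | 0.271 | 0.613 | 2.26 |
| 0.20 | 0.488 | 0.866 | 1.77 |
| 0.50 | 0.875 | 0.998 | 1.14 |

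**3. Only half the sessions still to come when the event occurs (k = 6 against 3).** The ratio reduces to 1 + (1 − q)^3, which is 1.86, 1.73 and 1.51 for q = 0.05, 0.10 and 0.20.

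**4. Other routes added.** Let p0 be the probability that an event is found in either arm by any route other than the sessions. Intervention: 1 − (1 − p0)(1 − q)^6; control: p0. For q from 0.02 to 0.20:

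| p0 | Ratio |
|---|---|
| 0.8 | 1.03 to 1.18 |
| 0.5 | 1.11 to 1.74 |
| 0.3 | 1.27 to 2.72 |
| 0.1 | 2.03 to 7.64 |

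Values above 2.83 arise only in the last row, where all other routes together find one event in ten and each session discloses at 0.05 or more (3.38 to 7.64).

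**5. A repair that would fail.** Suppose the by-arm count kept only events that first surfaced at common contacts. Take three sessions before the month-2 visit and consider that visit alone. The intervention count is then q(1 − q)^3 against q in control, a ratio of (1 − q)^3 = 0.86, 0.73 and 0.51 for q = 0.05, 0.10 and 0.20. With equal true rates that is a false deficit of 14%, 27% and 49%.

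**6. A repair that works.** Ask the same question at the common visits and count every event reported there, whether or not it was already known. Both arms then have 1 − (1 − q)^3, a ratio of 1.0, provided q is the same in both arms.

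**The case against.** Much can be said for the plan.

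- A reader might infer that more AEs *will* be found in the SFI arm. The text does not go that far. The observer attends to score fidelity, and the checklist is not said to collect AEs. Those whose reports open a form (child, parent/carer, teacher) exist in both arms.
- A reader might infer that the prompts go to intervention schools only. AEs procedures does not confine either the teacher alert or the encouragement to one arm. The imbalance lies in the word *related* and in the sessions.
- A reader might set four contacts (three sessions and month 2) against one and obtain a ratio of about 3 to 4. That leaves out the month 6 and 12 visits and all spontaneous reporting, which is the plan's stated route. It is not a supportable estimate.
- A reader might infer that a formal AE comparison between arms is planned. Statistical analysis names none and says that establishing differences between arms is not the study's purpose. Each event is also judged for causality and expectedness.
- Symptom diaries, health service use (including admissions) and absence records are collected in both arms, so the imbalance should be smaller for events that lead to medical contact.
- The design of the AE form may sit in the full protocol.

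These points limit the certainty and the size. They do not make ascertainment equal. The article sets out AE detection in some detail, and what it fixes is uneven. Case-by-case causality assessment works only on events already reported. Because AEs count whatever their cause, a reader of the pilot will naturally set one arm's frequency against the other's.

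**Conclusion.** The concern stands as an expected direction of bias, not a certain one. AE ascertainment is likely to be more complete in the intervention arm, and an excess there could partly reflect detection. The size cannot be fixed from the document. It is roughly 1.0 to 2.8 if children disclose at three common visits as readily as in sessions, or if other routes find 30% or more of events. It is close to 1 if most events are reported anyway. These figures illustrate and do not bound the effect: they rest on assumed, independent disclosure probabilities and equal true rates. The sessions come early, so mainly early events are affected. The consequence is for how the AE frequency is read by arm; no stated analysis is invalidated.

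**What to change.** - In AEs procedures, delete *related* from the request to families, and state that teachers in both arms receive the same AE briefing at the same time.
- Add a source field to the AE form: SFI session, common follow-up contact, or other.
- Put the same short AE question in the existing follow-up questionnaire in both arms.
- Base any by-arm AE frequency on answers to that question, with the children asked it as the denominator. Count an event whether or not it was already disclosed in a session. Report all AEs by source alongside.
- Do not drop session-first events from the comparison; step 5 of the working shows the false deficit this would create.

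The cost is one tick-box, one question and a short briefing in six control schools. No visits, staff or children are added, and every event is still recorded and reported as now. One limit remains: the sessions may leave intervention children readier to answer the common question, so some imbalance could persist. The source field has to be in place before data collection, because the source of an event is hard to reconstruct later.

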### Data collection

Prior to randomisation, a baseline assessment will include a classroom-administered questionnaire (including EQ-5DY, health service use and smoking behaviour) to be completed by participating children, APQ and school absenteeism form to be completed by school teachers, lung function assessment and saliva sample collection by the research team for each child (table 1). Each child will also receive a respiratory symptoms diary with instructions on how to use it. Follow-up assessment will take place at 2, 6 and 12 months post-allocation involving only those children whose cotinine levels were indicative of SHS exposure at baseline. All assessments carried out at baseline will be repeated at the follow-up assessment except cotinine levels which will only be assessed at month 2.

### Qualitative evaluation

Teachers and head teachers (2 and 1 per school; 12 and 6 in total, respectively) from the six intervention schools will be interviewed once the SFI has been delivered. Semistructured interviews will explore the barriers and facilitators to delivering the different components of the SFI, including training and resource needs. Interviews will be conducted using a topic guide to ensure consistency, with flexibility to allow participants to generate naturalistic data on what they see as important. Where possible, the interviews will be conducted face to face at school. If this is not possible, then telephone interviews will be done. With the participants’ permission, interviews will be audio recorded digitally and transcribed verbatim with anonymisation of all personal data.

### Data management and archiving

Data will be initially collected in the form of a paper-based questionnaire. Containing no participants’ identifiable information, these will be collected by the research team and kept in a locked cupboard separate from the consent forms. Once a week, data will be entered in the trial database, which will be kept at a secure server. The paper copies will continue to be kept in a securely locked cupboard.

In line with the Data Protection Act and the Research Governance Framework for Health and Social Care Research, at the end of the trial, data will be securely archived by the University of York for a minimum of 5 years. Following authorisation from the sponsor, arrangements for confidential destruction will then be made. If an individual withdraws consent for their data to be used, it will be confidentially destroyed.

### AEs procedures

We are expecting a minimal number of adverse and no serious AEs (SAEs) during the study. SFI is an educational intervention and has been very well received in our previous studies^17^ without leading to any directly related AEs. Nevertheless, there will be a vigilant surveillance system in place for AEs occurring during the course of the trial with particular emphasis on identifying, recording, reporting and managing any SAEs. We will sensitise schoolteachers to look for signs of any AEs resulting from the interactions between children and their parents. We will also encourage children and parents to report any related adversities.

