#### Health service use

We will use a health service utilisation questionnaire previously used in the Muslim communities learning about secondhand smoke (MCLASS) trial,^23^ to collect the number and type of contacts with doctors/nurses, hospital admissions, pharmacy visits and antibiotic prescriptions. This information will be part of the baseline questionnaire but will also be assessed at all follow-up time points.

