##### Serious adverse event

A SAE is any clinical occurrence that:
Results in death of the participant;Is life-threatening, defined as an event in which the participant is at risk of death during the event. This does not refer to incidents that hypothetically might have led to death if the event worsened;Results in hospitalisation or prolongation of hospital stay;Results in persistent and/or significant disability and/or incapacity;Birth defect or congenital anomaly;Any medical condition that may not be life-threatening, disabling or resulting in hospitalisation but requiring medical or surgical intervention to prevent any of the above outcomes.

Please note that any planned surgery or medical procedure will not be considered as an SAE.

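### SAEs are defined as all-cause, but the surveillance prompts ask for related events only, and hospital admissions reported on the child questionnaire are not expressly checked for SAEs

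*Protocol article*

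**What the plan says.** **Definitions.** Under Adverse event, an untoward clinical event counts "regardless of a causal relationship to the study intervention". Under Serious adverse event, one criterion is "Results in hospitalisation or prolongation of hospital stay". The only carve-out is that "any planned surgery or medical procedure will not be considered as an SAE". Together these make every unplanned admission after enrolment an SAE, whatever caused it.

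**Expectation and prompts.** The AEs procedures section says: "We are expecting a minimal number of adverse and no serious AEs (SAEs) during the study". It supports this by noting that the intervention is educational and produced no directly related events before. It then promises vigilant surveillance. Teachers are to watch for events arising from dealings between children and parents, and families are encouraged to report related problems.

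**Reporting.** Under Detecting, recording and reporting, the research assistant completes an AE form for an AE that a child, parent, carer or teacher reports. SAEs go to the principal investigator within 24 h of detection. They go to the sponsors and the bioethics committee within three working days, and to all investigators and the steering committee chair within 3 days.

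**Admissions as an outcome.** The Health service use section uses a questionnaire "to collect the number and type of contacts with doctors/nurses, hospital admissions, pharmacy visits and antibiotic prescriptions". It forms part of the baseline questionnaire and "will also be assessed at all follow-up time points". The Data collection section describes the baseline instrument as a "classroom-administered questionnaire (including EQ-5DY, health service use and smoking behaviour) to be completed by participating children", to be repeated at months 2, 6 and 12, but only in children whose baseline cotinine indicated exposure. For the paper forms, Data management and archiving says: "Once a week, data will be entered in the trial database".

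**The concern.** The definition, the forecast and the prompts do not cover the same events. The definition is all-cause. The forecast of none is argued from the absence of related events, and the prompts to teachers and families are also limited to related events. A child admitted with pneumonia meets the SAE definition but fits neither prompt.

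That child may still record the admission on the health service use questionnaire. The article describes that form as outcome data and never says that anyone reads it for safety events. The admission could then be counted under health service use and be absent from the SAE log.

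Two things are at stake. The frequency and nature of AEs is one of the research questions listed in the Introduction, so an undercount would carry into planning for the definitive trial. And the sponsors, the bioethics committee and the steering committee chair might not receive events that the protocol itself makes reportable.

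**Working it through.** **Step 1: compare the scope of each element.**

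| Element | Section | Scope |
|---|---|---|
| AE definition | Adverse event | Any cause |
| SAE definition | Serious adverse event | Any cause, including hospitalisation; planned procedures excepted |
| Forecast of no SAEs | AEs procedures | Argued from no directly related events |
| Teacher prompt | AEs procedures | Events from child-parent interaction |
| Family prompt | AEs procedures | Related problems |
| AE form trigger | Detecting, recording and reporting | Any AE reported by child, parent, carer or teacher; questionnaire not mentioned |
| Enquiry about admissions | Health service use; Data collection | Any cause, by child questionnaire |

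The prompts are narrower than the definition. The one all-cause enquiry about admissions has no stated link to the AE form.

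**Step 2: the plan's own figure.** The forecast of zero SAEs comes with no rate or formula, so it cannot be reproduced. The nearby retention figure does reproduce, 120 × (1 − 0.20) = 96, but it does not bear on this point.

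**Step 3: plausible size.** Inputs from the documents are 360 children enrolled (Study participants) and at least 120 expected to be cotinine positive (Sample size). The annual risk p of an unplanned admission is not given. I assume a range of 0.1% to 5%, over 12 months, with independent children.

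Expected number admitted = n × p. Chance of at least one = 1 − (1 − p)^n.

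| Assumed p | n = 120: expected | n = 120: chance of ≥1 | n = 360: expected | n = 360: chance of ≥1 |
|---|---|---|---|---|
| 0.1% | 0.12 | 0.11 | 0.36 | 0.30 |
| 0.5% | 0.6 | 0.45 | 1.8 | 0.84 |
| 1% | 1.2 | 0.70 | 3.6 | 0.97 |
| 2% | 2.4 | 0.91 | 7.2 | >0.99 |
| 5% | 6.0 | >0.99 | 18 | about 1.00 |

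The two bases answer different questions. For a disagreement between questionnaire and SAE log, the base is about 120, because only those children receive the follow-up questionnaire. For the forecast of no SAEs, the base is 360, because AE reporting covers every participant.

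**Step 4: when would zero be the likelier result?** Setting (1 − p)^360 = 0.5 gives p = 1 − 0.5^(1/360) = 0.19%. Under the all-cause definition, no admission among 360 children is more likely than not only if the annual risk is below about 0.19%. Zero is therefore unlikely over most of the assumed range, but not excluded at its low end.

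**The case against.** The case on the other side is substantial.

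- **The route is unstated, not closed.** An AE form is required for any AE a child reports, and the child completes the questionnaire. An answer recording an admission can be read as such a report. This stands, so one cannot say that nothing would open an SAE form. But the article does not say so, and it leaves unclear when such an answer counts as detected.
- **The forecast is not a rule.** No definition or deadline depends on it, and the same section stresses identifying and reporting any SAEs. This stands too. The mismatch in the prompts remains.
- **This is a condensed article.** Who checks which page could well sit in the full protocol. That goes some way towards excusing the missing link. It does not excuse the mismatch between definition and prompts, which is in the printed text of an otherwise detailed safety section.
- **The forms can be traced and are reviewed.** The enrolment number is printed on every tool, and the trial manager, who classifies AEs, also oversees checks of the paper forms. Those checks are described as data quality checks, however, not as a search for SAEs.
- **The rate is assumed.** Children with serious conditions needing regular hospitalisation are excluded, which lowers it.

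A reader might infer that the 24 h limit will be broken, because follow-ups lie 4 and 6 months apart and data entry is weekly. The text does not support that: the limit runs from detection. Nor does the Health economics section plan to cost admissions for named illnesses in the pilot. It speaks of hospital visits, and its illness list concerns the full trial.

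**Conclusion.** The point holds as a mismatch that should be corrected. As written, active surveillance is narrower than the all-cause SAE definition, and the one all-cause source on admissions is not expressly tied to SAE reporting. The SAE count may be too low and may disagree with the admissions recorded in the same children. Among the roughly 120 children followed by questionnaire, about 0.1 to 6 would be admitted in 12 months. That range rests wholly on the assumed 0.1% to 5% annual risk, on full follow-up and on children being independent.

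A reader might go further and infer that the two counts are bound to contradict each other. The documents do not support this. It would take an unplanned admission that is recorded on the questionnaire and also missed by AE reporting, and no rate for either is given. Unequal counts would not by themselves show an error either: admissions reported at baseline predate the trial, planned procedures are not SAEs, and AE reporting covers all 360 children while follow-up questionnaires do not.

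**What to change.** 1. **AEs procedures.** Reconcile the forecast and the prompts with the all-cause definition. For example, expect no intervention-related SAEs while acknowledging that background admissions may occur, and ask teachers and families to report any untoward event, including hospital admission.
2. **Health service use, and Detecting, recording and reporting.** State that the research assistant checks the health service use answers when each follow-up questionnaire is collected. A post-baseline unplanned admission is then treated as a detected SAE, identified by the enrolment number, and the existing deadlines run from that moment.
3. **Reconciliation.** At each follow-up, compare unplanned post-baseline admissions in the children given the questionnaire with the SAE log, and explain any difference. Exact equality is not the aim, for the reasons given in the verdict.

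The cost is a few sentences and seconds per questionnaire, with no new data collection. The downside is a few SAE forms for admissions unrelated to the intervention.
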